### Outcomes

The primary endpoint is defined as the duration from registration to diagnosis of FRNS. Diagnosis of FRNS is based on relapse dates according to the ISKDC. In our study, FRNS is defined as two relapses within 6 months of initial remission, or four relapses within any 12-month period. This includes relapses during initial tapering treatment, but excludes relapses with spontaneous remissions. Relapse is defined as proteinuria 2+ or higher on dipstick analysis for 3 or more consecutive days or proteinuria 2+ or higher on dipstick analysis and serum albumin ≤2.5 g/dL. Immunosuppressant administration is prohibited in the protocol. If patients show SDNS or SRNS, they are treated as an event in the primary analysis. Data for patients who do not experience these events are considered censored at the last examination. Secondary endpoints are relapse-free period, the poportion of patients without relapses, the number of relapses per person/year, time to SDNS, time to SRNS, total prednisolone dose, and adverse events. Adverse events were recorded throughout the trial period and assessed using Common Terminology Criteria for Adverse Events v3.0. Serum mizoribine concentrations at trough and C3 are measured 1 month after administration of mizoribine to monitor safety and pharmacological effect.

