### Randomization

Patients are randomly assigned to either the standard PSL plus high-dose mizoribine combination, or standard PSL alone group in a 1:1 ratio. We use a minimization method stratifying by age (2–5 years or 6–10 years), sex, duration from initial remission to relapse (< 90 days or ≥ 90 days) and institution as adjustment (stratification) factors. Patients, their guardians, treating physicians, and individuals assessing outcomes and analyzing data are not blinded to the patients’ treatment assignments. Apart from the trial statistician and the data-monitoring committee, all treating physicians and other investigators remain blinded to the trial results until follow-ups are completed.

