### Procedures

For the standard PSL plus high-dose mizoribine group, mizoribine is administered at a dose of 10 mg/kg/day (maximum 300 mg/day) once daily after breakfast and continued for 2 years. Mizoribin is started within 7 days from the registration date. After 2-year administration or termination of this trial, dosage of mizoribine will be tapered every month and stopped within 3 months. In case of leukocytopenia or impaired renal function, mizoribine treatment will be tapered or stopped. PSL treatment for relapse during the observation period follows the ISKDC regimen.

The observation period is from the registration date to the completion or discontinuation date of this trial. Completion of study is defined as completing of 2-year administration. Patients who complete or discontinue this study will be followed-up.

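### Spontaneously remitting relapses are left out of the FRNS count in a trial where physicians, assessors and analysts know the arm, so the exclusion can bias the primary endpoint

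*Protocol article*

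**What the plan says.** The Outcomes section of the protocol article states: "The primary endpoint is defined as the duration from registration to diagnosis of FRNS". FRNS is a count of dated relapses: "FRNS is defined as two relapses within 6 months of initial remission, or four relapses within any 12-month period". The next sentence settles which relapses count: "This includes relapses during initial tapering treatment, but excludes relapses with spontaneous remissions".

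The relapse criterion rests on dipstick and albumin. "Relapse is defined as proteinuria 2+ or higher on dipstick analysis for 3 or more consecutive days" is one route; the other is the same dipstick level together with low serum albumin. Steroid-dependent and steroid-resistant disease also enter the primary analysis: "If patients show SDNS or SRNS, they are treated as an event in the primary analysis".

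On relapse treatment, the Procedures section says "PSL treatment for relapse during the observation period follows the ISKDC regimen", for the trial as a whole.

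On blinding, the Randomization section says that patients, guardians and treating physicians know the arm, and that "individuals assessing outcomes and analyzing data are not blinded" to it. The only blinding described concerns results: "all treating physicians and other investigators remain blinded to the trial results until follow-ups are completed", with the trial statistician and the data-monitoring committee excepted.

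**The concern.** The exclusion depends on something that happens after randomisation and after the relapse criterion has been met. An episode can remit spontaneously only while PSL has not been started, and the person who starts PSL knows the arm. Two routes to bias follow.

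- **Waiting.** If PSL tends to be started later in one arm, more qualifying episodes in that arm have the chance to remit untreated and drop out of the count.
- **Labelling.** Whether a given episode is called a spontaneous remission is judged by people who know the arm.

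The endpoint amplifies either route. FRNS needs two or four relapses inside a time window, so losing one episode can delay the event or cancel it. If the share of excluded episodes differs by arm for reasons other than drug effect, the log-rank test and the hazard ratio carry that difference.

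**Working it through.** **1. The plan's own figure.** The document gives no rate of spontaneous remission, so there is no stated figure for this point. Its sample size supplies the background and is not disputed here. Inputs (Statistical analyses): 50% FRNS at two years on control, HR 0.50, two-sided 5%, 80% power, 4 years of accrual and 2 of follow-up.

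- Events (Schoenfeld): 4 × (1.960 + 0.842)² / (ln 0.5)² = 65.4, so 66.
- Event probability with uniform accrual: 1 − (e^(−2λ) − e^(−6λ)) / (4λ). With λ = ln 2 / 2 = 0.3466 this is 0.729 on control. With λ = 0.1733 it is 0.490 on mizoribine. The mean is 0.610.
- N = 66 / 0.610, about 109. The Lakatos log-rank method gives 107.98, so 108, as stated. 108 / 0.90 = 120.

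**2. Why a lost relapse matters.** Assume no drug effect, Poisson relapses, two years of observation, 60 per arm, and the four-in-12-months rule. A rate of about 2.36 relapses per year gives 50% FRNS. Remove a share of relapses in the mizoribine arm only (an assumption) and approximate HR = ln(1 − p) / ln(0.5). For 10% removed:

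- FRNS falls to p = 0.418, so HR = ln(0.582) / ln(0.5) = 0.78.
- Events = 60 × (0.418 + 0.500) = 55.1.
- z = √(55.1 / 4) × 0.247 = 0.917.
- Chance of a significant result favouring mizoribine = Φ(0.917 − 1.960) = 0.149, against 0.025 nominal.

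The same steps give HR 0.89 and about 7% when 5% are removed, and HR 0.59 and about 47% when 20% are removed.

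**3. Simulation with exclusions in both arms.** No true effect, 60 per arm, 5% of relapses dropped on control and 15% on mizoribine (assumed shares), 1,000 to 2,000 trials per setting:

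| Relapse model | Apparent HR | False positives favouring mizoribine |
|---|---|---|
| Poisson, four-in-12-months rule | 0.76–0.77 | 16–17% |
| Frailty, four-in-12-months rule | 0.84 | 9–11% |
| Frailty at 2.2 relapses per year, document's FRNS rule | 0.88 | 7.7% |
| Gamma frailty (variance 0.5) plus SDNS/SRNS hazard of 0.17 per year | 0.91 | 5.6% |

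The last row treats SDNS and SRNS as untouched by the exclusion. Its assumed hazard means 1 − e^(−0.34) = 29% with such an event by two years. The simulation error of the 5.6% is √(0.056 × 0.944 / 1000) = 0.7 percentage points, so the excess over 2.5% is more than noise.

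**4. Where the effect vanishes.**

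- 5% against 10% in the last model: HR 0.97 and 2.9%, with simulation error 0.5 points, so about nominal.
- 10% in both arms, without SDNS/SRNS events: HR about 1.0 and 2.2% to 2.7%.

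The difference between arms does the harm, not the exclusion as such. If exclusion lowers the FRNS hazard equally in both arms by 10% to 20%, the cost is power only: from 80% to about 78% to 75% at N = 108.

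**The case against.** - **Objective criterion.** Relapse is defined by dipstick and albumin, FRNS follows from dates, and SDNS and SRNS are events in their own right. This stands against saying that unblinded judgement decides which primary events occur. It does not cover the exclusion, which turns on the course after the criterion is met.
- **Direction.** A reader might infer that physicians will wait longer in the mizoribine arm and so favour the tested drug. The document does not support this: it applies one relapse regimen throughout and says nothing about different waiting. The inference is plausible, since one arm has added immunosuppression and less steroid is a stated hope, but it is conjecture.
- **Real effect.** If mizoribine makes more episodes remit without PSL, fewer counted relapses is benefit and not misclassification. This stands. A raw difference in exclusions cannot separate the two.
- **Secondary endpoints.** On a plain reading the exclusion qualifies FRNS only, so relapse-free period, proportion without relapse and relapse rate may count every qualifying episode. They would help to expose a differential but do not reproduce time to FRNS.
- **Condensed article.** A definition of spontaneous remission or an adjudication procedure may sit in the full protocol, and their absence here is no finding. The stated exclusion and the stated unblinding remain. A definition alone would not stop PSL timing from depending on the arm.

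**Conclusion.** The point holds as a risk. The article states both that some episodes meeting its relapse definition are left out of the FRNS count and that those who treat, assess and analyse know the arm. Nothing else in the article removes the resulting opening for differential misclassification.

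The size is illustrative only. At assumed exclusion shares of 5% and 15% with no true effect, the apparent HR is about 0.76 to 0.91 and the false-positive rate about 6% to 17%, against 2.5%. The milder end belongs to the model closest to the protocol's full event definition, and a smaller gap in shares brings the rate back to about nominal. The documents do not support reading these figures as an estimate of bias in this trial, or concluding that a favourable result would be spurious. This is a cheap improvement, not a fatal flaw, and open-label treatment itself is not in question.

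**What to change.** Keep the primary endpoint as defined, and make these changes.

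1. Derive FRNS and the spontaneous-remission exclusion from dated dipstick, albumin and PSL-start records, with allocation masked until the relapse list is locked.
2. Pre-specify a sensitivity analysis of time to FRNS, with SDNS and SRNS still as events, that counts every episode meeting the dipstick or albumin definition whether or not it remitted spontaneously.
3. Report the number of excluded episodes by arm.
4. State that the superiority conclusion will be treated with caution if the two analyses differ materially. The sensitivity analysis should not replace the primary one, because that would change the endpoint and could move the 50% event rate behind the sample size.

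Step 1 removes labelling bias only, since PSL-start dates already reflect unblinded decisions. Steps 2 and 3 are what make any waiting effect visible. None of this sets a clinical rule or changes visits or sample size. The cost is slightly more analysis work, and the sensitivity analysis will count some transient proteinuria in both arms.

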### Statistical analyses

The primary analysis of this study is to examine the superiority of PSL plus high-dose mizoribine combination therapy compared to standard PSL alone therapy in the time to FRNS.

For the sample size determination, we based the hazard rate ratio (HR, the PSL plus high dose mizoribine treatment group to the PSL treatment group) on the two-year FRNS probability. We estimated 50% at two-year in the standard PSL treatment and postulated the HR of 0.50. The required sample size was calculated as 108 patients (54 per arm) under a two-sided alpha 5% and 80% power, if the patients accrued for 4 years and follow up for 2 years. Considering withdrawal of consent or loss, target sample number was determined as 120 cases (60 each). We used POWER procedure of SAS software (version 9.3) for this calculation.

The primary endpoint, time to FRNS will be compared between these two groups using log-rank test. Cox proportional hazard model is used to estimate the hazard ratio with a 95% confidence interval. Kaplan-Meier method is used to summarize time to FRNS. The statistical significance level is set to 5%.

Secondary endpoints of relapse-free period and duration shifting to SDNS or SRNS will be compared in a similar manner as primary endpoint. The proportion of patients without relapses will be compared by Fisher’s exact test. Number of relapse and total steroid dose will be analyzed by Wilcoxson test. Correlation between mizoribine dose and blood concentration of mizoribine will be evaluated by Spearman rank correlation coefficient analysis.

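### The 108-patient, 80% power figure needs 2 to 6 years at risk per child, while the defined observation period ends at 2 years; on that definition, power under the stated inputs is about 61%

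*Protocol article*

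**What the plan says.** The Statistical analyses section gives the planning inputs: "We estimated 50% at two-year in the standard PSL treatment and postulated the HR of 0.50". The result is: "The required sample size was calculated as 108 patients (54 per arm) under a two-sided alpha 5% and 80% power", on the condition "if the patients accrued for 4 years and follow up for 2 years". The target is then raised to 120 to cover withdrawal of consent and loss. The calculation was run in the SAS POWER procedure, and the primary test is the log-rank test.

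The Procedures section sets the window for each child: "The observation period is from the registration date to the completion or discontinuation date of this trial", and "Completion of study is defined as completing of 2-year administration". After the 2 years, "dosage of mizoribine will be tapered every month and stopped within 3 months". The same section says that children who complete or discontinue will be followed up, but gives no length, schedule or closing date.

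The Outcomes section censors children without an event at their last examination. It names neither a 24-month cut nor a common closing date.

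**The concern.** In a log-rank calculation, an accrual period followed by a further follow-up period normally means that everyone is followed to one calendar date. With 4 plus 2 years, the first child contributes up to 6 years, the last child 2, and the average child 4. The Procedures section defines a window that closes after 2 years of administration. If that window governs the primary analysis, many of the events behind the 80% are never observed.

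If the later follow-up does count, the calculation needs the full effect to continue for up to 4 years beyond the 2-year treatment course. The article offers no argument for that.

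At stake is how a null result is read. A trial described as having 80% power has a 20% chance of missing the assumed effect. On the observation period as defined, that chance is about 39% with 108 evaluable children and 35% with 120 and no losses.

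**Working it through.** **Inputs** (protocol article, Statistical analyses and Randomization): two-sided alpha 5%, power 80%, control event probability 50% at 2 years, HR 0.50, 1:1 allocation, accrual 4 years, follow-up 2 years. Assumed, as the stated calculation implies: exponential times, proportional hazards, uniform accrual. Also assumed: 2 years in both arms, since completion of administration is literally defined only for mizoribine.

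**Hazards.** Control: ln 2 / 2 = 0.3466 per year. Mizoribine: 0.5 × 0.3466 = 0.1733 per year.

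**Events needed (Schoenfeld).** 4 × (1.960 + 0.842)² / (ln 0.5)² = 65.3.

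**Step 1: reproduce 108.** With uniform accrual over A = 4 years and a closing date F = 2 years after the last entry, the event probability at hazard λ is 1 − [exp(−λF) − exp(−λ(A+F))] / (Aλ).

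- Control: 1 − (0.500 − 0.125) / (4 × 0.3466) = 0.729.
- Mizoribine: 1 − (0.707 − 0.354) / (4 × 0.1733) = 0.490.
- Mean 0.610, so N = 65.3 / 0.610 = 107.2, rounded up to 108.
- Expected events at N = 108: 108 × 0.610 = 65.8.

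A Lakatos-type log-rank calculation, the kind of method the POWER procedure uses, gives 79.8% power at 108. Simulation (20,000 runs) gives 79.9%. The Freedman formula gives 116 on this reading.

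**Step 2: other readings.** A total duration of 4 years (2 to 4 years per child) needs 126. A fixed 2 years per child needs 165 (Schoenfeld), 172 (Lakatos) or about 180 (Freedman). Of the readings tested, only 2 to 6 years per child gives 108.

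**Step 3: 2 years per child.** Event probabilities are 0.500 and 1 − 0.5^0.5 = 0.293, mean 0.396.

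| N | Expected events | Lakatos | Schoenfeld | Freedman | Simulation |
|---|---|---|---|---|---|
| 108 | 42.8 | 60.7% | 62.1% | 58.8% | 61.6% |
| 120, no losses | 47.6 | 65.2% | 66.7% | 63.3% | 64.9% |

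For example, Schoenfeld at N = 108: √42.8 × 0.693 / 2 − 1.960 = 0.308, and Φ(0.308) = 0.621.

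The HR detectable with 80% power is then about 0.40 (N = 108) or 0.43 (N = 120).

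**Step 4: follow-up to a common close, with a weaker effect after year 2** (Lakatos, N = 108; the later HRs are assumptions, since the article gives none).

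| HR after year 2 | Power |
|---|---|
| 0.50 | 80% |
| 0.6 | 72% |
| 0.7 | 64% |
| 0.8 | 56% |
| 1 | 40% |

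If the effect fades enough, longer follow-up gives less power than stopping at 2 years, because the later events dilute the comparison.

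**Step 5: sensitivity to the control rate** (2 years per child, HR 0.50, Lakatos).

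| Control events at 2 years | N = 108 | N = 120, no losses |
|---|---|---|
| 40% | 50% | 55% |
| 50% (stated) | 61% | 65% |
| 60% | 70% | 74% |
| 70% | 77% | 82% |

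About 73% would be needed for 80% power at 108.

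**The case against.** The arithmetic of 108 is sound for the design it describes, and the article can be read as describing that design. Completers are to be followed up, the only censoring rule for the primary endpoint is the last examination, and accrual plus follow-up is the usual form for a common closing date. The phrase about the observation period appears in the section on treatment, not in those on outcomes or analysis. A condensed article may also leave the data cut-off to the full protocol.

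Much of this stands. A reader might infer that the plan certainly observes each child for only 2 years and that the trial's true power is therefore 61%. The documents do not support that: no sentence truncates the primary analysis at 24 months.

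It is also fair that 50% may be low. The Background gives 40 to 50% shifting to frequent relapse or steroid dependence among steroid-sensitive patients generally. This trial enrols children described as high risk and counts steroid dependence and resistance as events. Step 5 shows how much a higher rate would help, but the article plans on 50% and establishes nothing higher.

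What does not stand is that silence alone is at issue. The article defines when observation ends, and the sample size relies on time beyond that point. Nor does the common-close reading rescue the 80% by itself, because it also needs the HR to stay at 0.50 after mizoribine is withdrawn.

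**Conclusion.** The concern holds as a conflict between the sample-size calculation and the defined observation period, left unresolved by the censoring rule. The 80% is valid only with 2 to 6 years at risk per child and an HR of 0.50 persisting off treatment. On the observation period as defined, and under the stated inputs, power is about 61% with 108 evaluable children (59 to 62% across methods). The 65% at 120 is a ceiling, because the 12 extra children are there to absorb losses.

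A reader might also take 40% as the power under longer follow-up. That is the extreme case, in which the effect vanishes abruptly at year 2; an HR of 0.7 after year 2 gives about 64%.

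Confidence is high in the arithmetic and in the mismatch. It is lower on which follow-up the sponsor intends, because the article does not settle it.

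**What to change.** State one censoring rule for the primary endpoint, the same in both arms, and make the Procedures, Outcomes and Statistical analyses sections agree with it. Two routes are open:

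- **(a) Censor at 24 months from registration.** Restate about 43 expected events and 61% power for HR 0.50 with 108 evaluable children (at best about 48 events and 65% with 120 and no losses), or equivalently 80% power for an HR of about 0.40 to 0.43. Report later follow-up as a labelled secondary analysis.
- **(b) Follow all children to a common closing date.** Say that this follow-up counts in the primary analysis, and restate power with allowance for a weaker effect after treatment stops: at N = 108, 80% if the HR stays at 0.50, about 64% if it is 0.7 after year 2, and about 40% if it is 1.

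Either route means rewording the sample-size paragraph and adding a sentence on censoring. Neither needs extra enrolment. The cost is a less favourable stated power, except under (b) if a lasting effect can be justified.

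### The primary log-rank test and Cox model name none of the minimisation factors; to the extent that these factors are prognostic, the plain test is mildly conservative and gives up some power

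*Protocol article*

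**What the plan says.** Under Randomization, patients are allocated 1:1, and the method is described as "We use a minimization method stratifying by age (2–5 years or 6–10 years), sex, duration from initial remission to relapse" (cut at 90 days), with "institution as adjustment (stratification) factors" closing the list. There are therefore four factors.

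Under Statistical analyses, "The primary endpoint, time to FRNS will be compared between these two groups using log-rank test" and "Cox proportional hazard model is used to estimate the hazard ratio with a 95% confidence interval". Neither sentence names a stratum or covariate. The secondary time-to-event endpoints are to be compared in a similar way, so the point applies to them too.

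Under Outcomes, "FRNS is defined as two relapses within 6 months of initial remission, or four relapses within any 12-month period". Eligibility requires a relapse within 6 months of the first remission.

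The design assumptions are "We estimated 50% at two-year in the standard PSL treatment and postulated the HR of 0.50" and "The required sample size was calculated as 108 patients (54 per arm) under a two-sided alpha 5% and 80% power", with 4 years of accrual and 2 years of follow-up. The target is 120 after allowing for losses.

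**The concern.** Minimisation makes the arms more alike on the chosen factors than simple randomisation would. If those factors predict the outcome, the true variance of the treatment comparison is smaller than a plain log-rank test assumes. The test then rejects less often than 5% under the null and has less power than one that uses the factors. The unadjusted hazard ratio also lies closer to 1 than the within-stratum ratio.

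Time to relapse deserves particular attention. On the natural reading of the FRNS definition, every child enters with one relapse already counted. A child who first relapsed at 30 days has about five months left in which one further relapse is an event. A child who relapsed close to 6 months has almost no window left and needs three more relapses within 12 months of the first. The <90/≥90-day factor would then predict the endpoint even if both groups relapsed at the same underlying rate.

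What is at stake is a missed effect in a trial of 120 children, not a false claim of benefit.

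**Working it through.** **1. The plan's own sample size.** Exponential hazards: control ln2/2 = 0.3466 per year, mizoribine half of that, 0.1733. With uniform accrual over 4 years and 2 further years of follow-up, the event probability is 1 − (e^(−2λ) − e^(−6λ))/(4λ).
- Control: 1 − (0.500 − 0.125)/1.386 = 0.729.
- Mizoribine: 1 − (0.7071 − 0.3536)/0.693 = 0.490.
- Mean: 0.610.

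Schoenfeld events: 4 × (1.960 + 0.842)² / (ln 0.5)² = 65.3, so 66. Then 66/0.610 = 108.2, which matches the stated 108. The calculation is for a plain log-rank test and makes no allowance for prognostic factors.

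**2. Is time to relapse prognostic?** The article gives no effect size. As an illustration, one Poisson relapse rate was applied to both groups and the FRNS definition was imposed, ignoring SDNS and SRNS events. The implied ratio is ln(1 − p₁)/ln(1 − p₂), the ratio of 2-year cumulative hazards. Two sets of runs gave different levels but the same direction.

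| Assumed relapses per year | 2-year FRNS, <90 v ≥90 days | Implied ratio |
|---|---|---|
| 1 | 34% v 18% | 2.1 |
| 1.5 | 52% v 35% | 1.7 |
| 2 | 67% v 53% | 1.5 |
| 1 (second set) | 31% v 14% | 2.5 |
| 2 (second set) | 60% v 44% | 1.6 |

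A hazard ratio around 1.5 to 2.5 for this factor is therefore plausible from the definition alone.

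**3. Effect on the test under the stated design.** Simulation with N = 108, the planned accrual and follow-up, control 2-year risk held at 50%, treatment HR 1 or 0.50 within strata, and 10,000 runs per scenario (standard error about 0.4 points for power and 0.2 for type I error). Assumed, because the article does not give them: biased coin 0.8, 20 institutions with no effect on hazard, factor prevalences 0.5/0.35/0.5, and the prognostic HRs. The adjusted Cox model contains age group, sex and time to relapse.

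| Prognostic HRs | Plain log-rank: type I / power | Adjusted Cox: type I / power | Power difference | 8-stratum log-rank power |
|---|---|---|---|---|
| 1.0 each | 5.3% / 80.0% | 5.6% / 79.8% | −0.2 | 74.7% |
| 1.25 each | 4.8% / 78.2% | 5.5% / 79.7% | 1.5 | 74.2% |
| 1.5 each | 4.0% / 75.8% | 5.0% / 79.4% | 3.6 | 73.9% |
| Time to relapse only, 2.0 | 4.2% / 75.7% | 5.3% / 79.2% | 3.5 | 73.7% |
| 2.0 each | 3.5% / 69.2% | 5.3% / 78.7% | 9.5 | 73.0% |

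The adjusted Wald test runs at 5.0 to 5.6%, so a small part of its advantage reflects slight liberality. The unadjusted HR estimate moves from 0.50 to 0.54 as the factor HRs rise to 2.0 each; the adjusted one stays at 0.49.

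**4. Coarser strata.** N = 108, 3,000 runs (standard error 0.8 to 0.9 points). With only time to relapse prognostic at HR 2, power was 75.3% plain, 79.1% stratified by time to relapse, and 77.6% stratified by time to relapse × age. With no prognostic effect, time to relapse × age strata gave 78.3% against 80.4% plain.

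**5. N = 120 with everyone censored at 2 years.** With time to relapse alone at HR 2, power was about 65% plain and 67% stratified by time to relapse or adjusted. With HRs of 2 (time to relapse), 1.5 (age) and 1.3 (sex), two sets of runs gave 64.9% v 67.2% and 62.7% v 64.7%, plain v stratified. With no prognostic effect they gave 67.4% v 66.6% and 65.9% v 65.6%.

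**The case against.** The strongest reply is that the article is silent rather than wrong. It never says that the test is unstratified or the model unadjusted, and a condensed article may leave covariates to an analysis plan that is not shown. It is true that the text does not rule adjustment out. But the primary test and the estimator are both stated, no factor appears in either, and the factors are already used in allocation. A better-specified test at almost no cost can be recommended on what is written.

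Second, the loss depends on prognostic strength that no section supplies. The article calls relapse within 6 months a risk factor, but every enrolled child meets that criterion, so it says nothing about <90 against ≥90 days. This stands. The FRNS definition makes an effect of time to relapse likely but does not fix its size, and there is no comparable argument for age or sex.

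Third, part of the apparent loss comes from fixing HR 0.50 within strata. When marginal 2-year risks were held at 50% and 29% instead, plain-test power was 66.9%, 66.6%, 65.8% and 66.4% across four scenarios from no prognostic effect to HRs of 2/1.5/1.3 (N = 120, 2-year follow-up). Measured against the planned power, the loss then nearly vanishes. This stands too, and a marginal hazard ratio is a legitimate target. It does not address whether a test that uses the factors would do better on the same data.

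Fourth, stratifying finely can hurt: the 8-stratum test had less power than the plain test in every scenario above except HR 2.0 for all three factors. This bears on the form of the remedy, not on the point itself.

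**Conclusion.** The point holds as a modest, conditional efficiency loss. As written, the primary analysis uses none of the four allocation factors. Where those factors are prognostic, the plain log-rank test is mildly conservative. The power given up is about 0 to 2 points at weak effects and about 2 to 6 points at prognostic HRs near 2. The 9.5-point gap in the working needs age, sex and time to relapse all at HR 2 together, which nothing in the article supports. All these sizes rest on assumed prognostic HRs, prevalences, number of institutions and coin probability.

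A reader might infer three stronger things:
- **That the planned test is invalid.** It is not. The error is toward too few rejections, so a positive result would stand.
- **That a loss is certain.** It is not. With non-prognostic factors the plain test keeps about 5% type I error and 80% power under the stated design.
- **That the roughly 65% power seen with 2-year censoring is caused by omitting the factors.** It comes from the shorter follow-up, which is a separate question; under the stated accrual and follow-up, 108 patients reproduces.

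**What to change.** Add one sentence to Statistical analyses, settled before outcome data are compared by arm, choosing one of two primary tests:
- a log-rank test stratified by time from initial remission to relapse (<90 or ≥90 days); or
- the treatment test from a Cox model adjusted for time to relapse, age group and sex.

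In either case, report the hazard ratio and 95% confidence interval from that adjusted Cox model, and give the unstratified log-rank result as supportive. Do not stratify finely by institution or by the full cross-classification of factors, because small strata lose information. Use the same approach for the secondary time-to-event endpoints.

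The factors are already collected at registration, so no new data are needed. The price is at most about 1 point of power if the factors turn out not to be prognostic, and a hazard ratio that is conditional on the factors and should be described as such.

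### Fisher's exact test on the proportion without relapse cannot use partial follow-up; a 24-month Kaplan-Meier comparison would suit this secondary endpoint better (minor)

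*Protocol article*

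**What the plan says.** The Outcomes section lists two endpoints built from the same first-relapse information: "Secondary endpoints are relapse-free period, the poportion of patients without relapses".

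The Statistical analyses section treats them differently. The first is analysed with censoring: "Secondary endpoints of relapse-free period and duration shifting to SDNS or SRNS will be compared in a similar manner as primary endpoint". For the primary endpoint, "time to FRNS will be compared between these two groups using log-rank test", with a Cox model and Kaplan-Meier curves alongside. The second is reduced to a binary outcome: "The proportion of patients without relapses will be compared by" Fisher's exact test.

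Incomplete follow-up is expected: "Considering withdrawal of consent or loss, target sample number was determined as 120 cases (60 each"), up from the calculated 108. The Procedures section runs observation from registration to completion (two years of administration) or discontinuation. It also says that children who complete or discontinue will be followed up.

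For the primary endpoint the Outcomes section gives a censoring rule: "Data for patients who do not experience these events are considered censored at the last examination". The article gives no corresponding rule for the binary endpoint.

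**The concern.** Fisher's test needs a yes or no for every child it includes. A child who leaves at two months without a relapse has no two-year status, so that child must be counted as relapse-free, counted as relapsed, or dropped. The Kaplan-Meier method avoids the choice: the child contributes two months and is then censored.

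Three things are at stake:

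- the relapse-free percentage itself, which readers are likely to quote;
- some power;
- consistency, because the binary result and the log-rank result describe the same outcome and could differ only because of how lost children were handled.

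**Working it through.** **The plan's own figures.** Events needed for the primary comparison: 4(1.960 + 0.842)² / (ln 0.5)² = 65.3, rounded up to 66. With a 50% two-year control rate, hazard ratio 0.50, four years' accrual and two further years, the mean event probability is 0.610, and 65.3 / 0.610 gives 108 after rounding up. Then 108 / 0.90 = 120, so the allowance is 12/120 = 10%. These figures concern the log-rank test on time to FRNS. No power is stated for the Fisher comparison.

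**Inputs for the check.**

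- 60 per arm (Statistical analyses).
- Two-year relapse of 80%, so S = 0.20 relapse-free. The Background gives this for steroid-sensitive disease in general; applying it to this early-relapse population is an assumption.
- A hazard ratio of 0.6 for relapse, and all splits of loss between arms, are assumptions.
- Relapse and loss times are exponential. Loss d is the two-year probability of loss in the absence of relapse.

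**Expected proportions.** Let λ = −ln(S)/2 and μ = −ln(1−d)/2.

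- Lost before relapse: L = μ/(μ+λ) × [1 − S(1−d)]
- Observed relapse-free to two years: K = S(1−d)

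With S = 0.20 and d = 0.10: λ = 0.805, μ = 0.0527, L = 0.0614 × 0.82 = 0.050 (about 3 children per arm), K = 0.180.

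- Lost counted as relapse-free: K + L = 23.0%
- Lost excluded: K/(1−L) = 0.180/0.950 = 19.0%
- Lost counted as relapsed: K = 18.0%

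The truth is 20.0%. For control relapse of 70% (truth 30%) the first two rules give 32.9% and 28.7%. For 90% (truth 10%) they give 13.0% and 9.4%.

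**Difference between arms, hazard ratio 0.6, 10% loss in each arm.** True relapse-free in the mizoribine arm is 0.20^0.6 = 38.1%, a true difference of 18.1 points. The same formulas give 40.7 − 23.0 = 17.7 (relapse-free), 36.6 − 19.0 = 17.6 to 17.7 (excluded) and 34.3 − 18.0 = 16.3 points (relapsed). Equal loss moves the difference little.

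**Power and type I error.** Fisher's test was evaluated by exact binomial summation where lost children are counted one way or the other. The other figures come from simulations of 4,000 to 6,000 trials per setting (Monte Carlo error below 1 point). Ranges span the runs.

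| Setting (control / mizoribine loss) | Fisher, lost = relapse-free | Fisher, lost excluded | Fisher, lost = relapsed | Kaplan-Meier difference |
|---|---|---|---|---|
| HR 0.6, 10% / 10% (power) | 45–47% | 51% | 44–45% | 58% |
| HR 0.6, 5% / 25% (power) | 73% | 35–37% | 17% | 56–57% |
| No effect, 10% / 10% (type I) | 2.9% | about 3% | 2.8% | about 5–6% |
| No effect, 5% / 25% (type I) | about 9% (exact 8.7%) | about 4% | about 5% | about 5–6% |

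The log-rank test has about 62 to 63% power in both HR 0.6 settings. The Kaplan-Meier estimates stay on target throughout (about 20% and 38%).

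**How much of the gap is conservatism.** In the first row with lost children counted as relapse-free, an uncorrected chi-square test on the same proportions has 56% power against Fisher's 47% (exact). So much of the gap to Kaplan-Meier under that rule comes from Fisher's actual size of about 3%, not from discarding follow-up time.

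**Within the plan's allowance.** A 5% / 15% split still averages 10%. Counting lost children as relapse-free, Fisher's exact type I error is then 4.2%.

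**The case against.** A reader might infer that the plan scores lost children as relapse-free. The article does not say so and Fisher's test does not impose it. The rule may stand in the full protocol or analysis plan, so its absence here is not itself the finding. What remains is that a named test forces some such rule, and the simple ones either bias the proportion or depend on how loss is split.

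A reader might also infer an inflated type I error. That needs the relapse-free rule together with losses such as 5% versus 25%, which average 15% and exceed the 10% allowance. With equal loss Fisher's test is conservative.

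Nor do the documents support predicting which arm loses more. The trial is open-label, so either arm could; the article describes mizoribine as milder than other immunosuppressants. The stated follow-up after discontinuation could reduce the loss, though the article does not say whether those data enter this endpoint.

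The power comparison is not quite like for like, since it sets a conservative test against a slightly liberal one, and a hazard ratio of 0.6 for relapse is not the plan's figure. No power is claimed for this endpoint.

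The strongest objection is that the log-rank analysis of relapse-free period already uses the same information efficiently. That stands and keeps the severity low. It also means that the Fisher result adds a second, weaker test of the same question.

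**Conclusion.** The concern holds as a minor point. The stated method cannot use partial follow-up in a trial that expects about 10% loss. At that loss in each arm, and a true 20% relapse-free, the reported proportion would be off by about 3 points upward or 1 to 2 points downward, depending on the rule, with little effect on the difference between arms. Power at an assumed hazard ratio of 0.6 is about 44 to 51%, against about 58% for the Kaplan-Meier difference; part of this is Fisher's conservatism. Only under strongly unequal loss does the choice of rule dominate, moving Fisher's power between 17% and 73%.

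These sizes rest on the general 80% relapse rate, exponential times, loss unrelated to prognosis, and assumed loss splits. The primary endpoint, its log-rank test and the sample size are not touched.

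**What to change.** In the Statistical analyses section, replace Fisher's test by the Kaplan-Meier relapse-free probability at 24 months in each arm and their difference with a 95% confidence interval (Greenwood or log-log variance). Keep the log-rank test on relapse-free period, already planned, as the only test of this outcome.

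The cost is one line of wording, with no new data and no change in sample size. The downside is that the Wald interval is slightly liberal at 60 per arm, with an error rate of about 5 to 6% against the nominal 5%. This matters little if the interval serves as an estimate and the log-rank test carries the inference.
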